### Risk management and mitigation

There are no foreseeable risks to participating in the online study as we will not collect any biomarker specimens, provision of interventions or treatments, or clinical recommendations to participants. Participants volunteer and consent to participate in the study and can withdraw at any time. The study will stop once the total estimated sample size of 10,000 study participants is reached; and a total sample size of 1,000 study participants for the pilot study. The participants may not directly benefit from this research. However, we hope that the results of the study will inform future vaccination efforts which may indirectly have broader population benefits.

### Data collection

The Gorilla platform will be used to collect data. By clicking on the response buttons, participants will submit data. We will conduct a pilot phase for the duration of 4 weeks (currently planned for May 2022); the full trial is estimated to last 3 months (currently planned for June to August 2022) or until 10,000 study participants have been recruited, whichever comes first. The overview of the study timeline for our project is depicted in Table 2.

**Table 2 T2:** Overview of study timelines.

**Item**	**Month**											
	**1**	**2**	**3**	**4**	**5**	**6**	**7**	**8**	**9**	**10**	**11**	**12**
Develop protocol												
Obtain ethical clearance												
Register trial with pre-analysis plan												
Publish protocol paper												
Conduct pilot study												
Conduct data analysis pilot study												
Prepare and publish pilot study manuscript												
Revise full study based on pilot study findings												
Conduct full study												
Conduct data analysis pilot study												
Prepare and publish full study manuscript												

### Data management

Each study participant will be allocated a unique, anonymous string identifier. The identifier will be linked to the participant's responses on the Gorilla platform. Participants' unique identifiers will be devoid of any identifying information. The trial data will be stored on Gorilla's cloud platform, which is hosted on Microsoft Azure in the Republic of Ireland. The study investigators will retain ownership of the research data produced. The Gorilla platform enables research investigators to generate and access anonymized data. The data will be downloaded and safely stored in a computing system maintained by the University of Heidelberg. Data will be stored for 10 years (and afterwards deleted) on secured University servers of HIGH, according to good scientific practice.

Our third objective is to determine whether study participants in the non-intervention arms are willing to voluntarily engage with the SAS video about the COVID-19 vaccine at the end of the study. The decision to view the SAS video and the duration of time spent watching the SAS video will be used to determine participant engagement. We will create a dummy variable that equals 1 when the participant clicks the “Play” button to view the SAS intervention video and 0 when the participant chooses to skip the SAS intervention video and click “Finish” the study to assess the participant's willingness to watch the SAS intervention video. We will employ a logistic approach to measure the sociodemographic parameters that influence the decision to watch or not watch the intervention video post-trial:

(3)
$$\begin{array}{r} WatchVideo_{i}=\gamma_{0}+\gamma_{1}VideoArm_{i}+\gamma_{2}X \end{array}$$

where *y*_*i*_ is a dummy variable which equals 1 when the participant clicks on the “Play” button to begin watching the SAS intervention video and 0 otherwise, *VideoArm*_*i*_ indicates the *k*th arm, *X* is a vector of covariates.

Among the participants who will choose to watch the SAS intervention video, we will quantify the length of time that they will spend watching the SAS intervention video using the timestamps provided by Gorilla's graphical experiment builder. We will use ordinary least squares (OLS) regression models to investigate which sociodemographic factors were associated with engagement time.

(4)
$$\begin{array}{r} EngagementTime_{i}={\text{λ}}_{0}+{\text{λ}}_{1}VideoArm_{i}+{\text{λ}}_{2}X \end{array}$$

where *EngagementTime*_*i*_ is the length of time participant *i* spent watching the SAS intervention video reported in seconds (min = 0, max = 1,800), *VideoArm*_*i*_ indicates the *k*th arm, *X* is a vector of covariates.

Regarding our second objective, we will explore the differences in individual factors related to the levels of vaccine hesitancy between the vaccinated and unvaccinated study participants. To do so, we will first compute a comprehensive score for each individual factor which are: perception of risk and benefit, attitude, self-efficacy, perceived social norms, and trust. We will then inspect correlations between such factors and participants' vaccination status using OLS models.

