
As part of this study, we prepared a collage of three SAS videos about the COVID-19 vaccine with no audio (just sound effects and background music) that illustrate the importance of getting vaccinated against COVID-19. The employed SAS videos incorporate a variety of audience engagement methods, including culturally agnostic characters and an emotionally compelling soundtrack, that may encourage more users to share the videos on social media (22). We will evaluate the effectiveness of the SAS videos in increasing knowledge about the COVID-19 vaccination, as well as the impact of the SAS videos in changing attitudes and behavioral intent to get vaccinated and learn more about the COVID-19 vaccine. Additionally, we will examine the degree of participants' voluntary involvement, as defined by their willingness to view the SAS videos and the duration of time spent completing the task in the non-intervention arms. Lastly, we will examine the differences in individual characteristics related with vaccine confidence between the three arms - such as hope, optimism, risk and benefit perception, self-efficacy, perceived social norms, and trust. Our findings will support others in developing simple yet effective health communication strategies to address vaccination hesitancy more effectively.

The primary objectives of this study are as follows:

To evaluate the SAS video's effectiveness in:

improving COVID-19 vaccine knowledge.increasing behavioral intent toward COVID-19 vaccine.quantifying intrinsic interest in watching a SAS video about COVID-19 vaccine.

The secondary objective of this study is to explore the differences in individual factors connected to vaccine hesitancy between the three study arms after the interventions, which are equally distributed across groups by randomization.

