### Outcomes

The primary outcome of this study is the effectiveness of the SAS intervention video in increasing knowledge about the COVID-19 vaccine. While knowledge alone is insufficient to modify health behaviors, it is vital for individuals to access and comprehend their health options in order to exert greater control over their health decisions (29, 30). Furthermore, as a second primary outcome, we will measure changes in behavioral intent toward the COVID-19 vaccination. According to the Theory of Planned Behavior (TPB), the intention to act is considered the immediate determinant of action. In this study, behavioral intent is defined as a participant's commitment to receive the COVID-19 vaccine and to seek information about the vaccine during the next two weeks (31). As a third primary outcome, we will evaluate participant willingness (quantification) to voluntarily engage with the SAS intervention videos (post-trial access to treatment) to determine whether SAS videos may have the potential to generate interest as a precursor for health promotion and communication.

As secondary outcomes, we will focus on COVID-19 risk and benefit perception, social norms, hope, and optimism that we hypothesize will change as a result of the intervention.

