#### Secondary outcome measures

Components of the complexity of vaccine hesitancy that have been identified in the research, namely COVID-19 risk and benefit perception, social norms, hope, and optimism, are secondary outcomes that we hypothesize will change as a result of the intervention. Therefore, all participants will be asked to complete questionnaires measuring their perceptions of severity and susceptibility, response efficacy, attitude, self-efficacy, social norms, as well as questions relating to optimism, hope, and trust.

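### The secondary objective compares the three randomised arms, but the only analysis stated for those factors relates them to baseline vaccination status and leaves out hope and optimism

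*Protocol article*

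**What the plan says.** **The objective.** The Introduction states the secondary objective as a comparison of arms: to "explore the differences in individual factors connected to vaccine hesitancy between the three study arms after the interventions". Earlier in the same section the factors to be compared are given as differences "between the three arms - such as hope, optimism, risk and benefit perception, self-efficacy, perceived social norms, and trust".

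**The outcomes.** The Outcomes section names as secondary outcomes "COVID-19 risk and benefit perception, social norms, hope, and optimism that we hypothesize will change as a result of the intervention". The section on secondary outcome measures repeats that these components "are secondary outcomes that we hypothesize will change as a result of the intervention".

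**The analysis.** Under Statistical methods for primary and secondary outcomes, the one paragraph on these factors says "we will explore the differences in individual factors related to the levels of vaccine hesitancy between the vaccinated and unvaccinated study participants". The factors to be scored are listed as "perception of risk and benefit, attitude, self-efficacy, perceived social norms, and trust". The next step is "We will then inspect correlations between such factors" and vaccination status, using OLS models. No equation is given for this step.

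**Other statements of the aim.** The Abstract lists hope and optimism among the factors and describes comparing vaccinated with unvaccinated participants across the three arms. The Discussion, under Principal findings, mentions only the vaccinated-versus-unvaccinated comparison.

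**The concern.** The objective and the outcome definitions ask a causal question that randomisation can answer: did the video change these factors? The analysis paragraph asks a descriptive one: how do people who were already vaccinated differ from those who were not? An analysis that followed this paragraph alone would not estimate the effect of the intervention on any secondary outcome, and would not score hope or optimism at all.

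This is more than detail left to an analysis plan. The article states an analysis, and that analysis targets a different contrast from the objective. A plan written from that paragraph would carry the mismatch forward. Arm comparisons added after the data had been seen would be post hoc.

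**Working it through.** **1. Set the sections side by side.**

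| Place | Comparison | Hope and optimism included? |
|---|---|---|
| Introduction, secondary objective and preceding text | Between the three arms | Yes |
| Outcomes; Secondary outcome measures | Change caused by the intervention | Yes |
| Abstract | Vaccinated vs unvaccinated, across the arms | Yes |
| Statistical methods | Vaccinated vs unvaccinated | No |
| Discussion, Principal findings | Vaccinated vs unvaccinated | Factors not listed |

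The four numbered models in the statistical methods (knowledge, behavioural intent, watching the video, engagement time) each carry an arm term. The text on the secondary factors mentions none. Of the four secondary outcomes named in the Outcomes section, two (hope and optimism) are missing from the list of scored factors.

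**2. Check what the stated analysis can estimate.** Trial design says that participants complete the vaccine survey before being randomly assigned. Vaccination status V is therefore a baseline variable, independent of arm. Let g be the vaccinated-minus-unvaccinated gap without any video, and let d be the effect of the SAS video, the same in both groups, on the one third of participants in arm 1. Take arm 2 as having no effect. Then

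E[score | V=1] − E[score | V=0] = (g + d/3) − d/3 = g.

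The effect d cancels. If the effect differs by status (d₁ in the vaccinated, d₀ in the unvaccinated), the result is g + (d₁ − d₀)/3. One coefficient cannot separate that sum into its parts. In neither case does it tell the reader whether the video worked.

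**3. Confirm by simulation.** Assumed inputs, none of them from the protocol: 300 trials of 9,999 participants in three equal arms, 80% vaccinated, a gap of 0.8 SD, and a uniform effect in arm 1 only (SD is the residual SD within vaccination status).

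| Assumed video effect (SD) | Mean vaccination-status coefficient | Mean arm 1 minus arm 3 |
|---|---|---|
| 0 | 0.80 | 0.00 |
| 0.1 | 0.80 | 0.10 |
| 0.3 | 0.80 | 0.30 |

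The vaccination-status coefficient is the same whether the video does nothing or has a clear effect. The arm difference recovers the effect each time.

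**4. Check whether the trial could answer the stated objective.** The protocol gives no power figure for the secondary outcomes, so there is none to reproduce. The inputs are 10,000 participants allocated 1:1:1, about 3,333 per arm, with two-sided alpha 0.05 and 80% power. The detectable pairwise difference is

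(1.960 + 0.842) × √(2/3,333) = 2.802 × 0.0245 = 0.069 SD.

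If 20% were lost (an assumption), leaving about 2,667 per arm, it is 2.802 × √(2/2,667) = 0.077 SD. The sample is large enough for the arm comparison; what is missing is the analysis statement.

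**The case against.** **The vaccinated-versus-unvaccinated comparison is an aim in its own right.** The Abstract and the Discussion both state it, so the analysis paragraph does answer one of the stated aims. This stands. The comparison is legitimate, but it cannot stand in for the objective in the Introduction, and the two statements of the aim need to be reconciled.

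**The complaint is partly an argument from silence.** No equation is written for these factors. The reference to a second objective is ambiguous, because the second primary objective is behavioural intent. The timeline table also mentions a registered pre-analysis plan that is not shown. It would therefore be too strong to say that the trial will produce no randomised estimate for any secondary outcome. What can be said is that the article's only analysis text on these factors, under a heading that covers primary and secondary outcomes, states none, and that its factor list reads as complete.

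**Arm contrasts are defined elsewhere.** Strengths and limitations defines total, content and attention effects without restricting them to primary outcomes. That is correct, and the fix uses those definitions. No stated analysis applies them to the secondary scores.

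**A stronger reading to avoid.** A reader might infer that the vaccinated-versus-unvaccinated association is distorted because the factors are measured after the video. The documents do not support this. As the working shows, a uniform effect leaves the association unchanged. Bias arises only if the effect differs by vaccination status, and nothing in the protocol says that it does or by how much. Nor can a hypothetical shift in that gap usefully be set against the detectable difference between two arms: they are different contrasts with different standard errors.

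**Conclusion.** The point holds as a mismatch between objective and analysis. The secondary objective and outcomes are framed by randomised arm. The only analysis stated for them is framed by a variable fixed before randomisation, has no stated arm comparison, and omits two of the four named secondary outcomes. As written, that analysis cannot show whether the video changed any secondary outcome.

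The conclusion rests on the text and on one assumption: that vaccination status means the status recorded at entry. The order of surveys in Trial design, the use of status for recruitment strata in Participants and its place in the sample description all support this. The simulation and detectable differences are illustrative and do not carry the conclusion.

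The primary outcomes are not affected. The change should be made before the data are analysed. The conclusion does not extend to saying that the vaccination-status association is biased, or that the vaccinated-versus-unvaccinated aim is improper.

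**What to change.** In Statistical methods for primary and secondary outcomes:

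- **Arm comparison.** For every secondary score, hope and optimism included, fit OLS on arm indicators, optionally with baseline covariates such as vaccination status. Report the three effects defined in Strengths and limitations, each with a 95% confidence interval: total (arm 1 vs arm 3), content (arm 1 vs arm 2) and attention (arm 2 vs arm 3).
- **Interpretation for hope and optimism.** State that the arm 2 video itself conveys hope, so it is not an inert comparator for these two scores. The arm 1 vs arm 2 difference does not isolate vaccine content there, and the contrasts with arm 3 matter more.
- **Vaccinated versus unvaccinated.** Keep this as a separate, exploratory analysis with arm terms. Add an arm-by-vaccination-status interaction, because pooling the arms could bias the comparison if the effect differs by status.
- **Consistency.** Align the Abstract, Introduction, Outcomes, analysis and Discussion on which comparison is the secondary objective and which factors it covers, and replace the ambiguous reference to a second objective.

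The cost is wording and a few more regressions. All the scores are already to be collected, and no change to design, sample size or questionnaires is needed.

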**Methods and analysis:**

We will conduct an online randomized controlled trial primarily to: (1) determine the effectiveness of SAS videos in improving COVID-19 vaccine knowledge; (2) evaluate the effectiveness of SAS videos in increasing behavioral intent for COVID-19 vaccination; and (3) quantify people's interest in watching SAS videos about the COVID-19 vaccine. We also aim to identify barriers and facilitators to COIVD-19 vaccinations that have been shown to minimize vaccine hesitancy between vaccinated and unvaccinated populations. Using a web-based recruitment platform, a total of 10,000 adults from the United States will be recruited and randomly assigned to (1) a SAS video collage arm, (2) an attention placebo control video arm, or (3) no intervention arm (1:1:1). Furthermore, we will measure behavioral intent to obtain information on vaccination regarding COVID-19. At the end of the trial, participants randomized to arm 2 and arm 3 will be given the option of watching one of the intervention videos voluntarily to assess participant engagement with SAS videos. Finally, we will assess individual factors associated with vaccine hesitancy - hope, optimism, COVID-19 perceived risks and benefits, self-efficacy, perceived social norms, and trust - and compare vaccinated and unvaccinated participants across the three arms.

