## Methods and analysis

### Trial design

We will conduct a randomized controlled trial (RCT) following a multi-site, parallel group design with post-trial access to treatment (see Figure 1). After completing demographic, vaccine, and political beliefs surveys, participants will be randomly assigned to one of three arms: an intervention arm exposing participants to the SAS video collage (arm 1), an attention placebo control (APC) arm showing a video of similar length unrelated to the vaccine (arm 2), or a control arm without any intervention (arm 3). We will randomize the participants in a 1:1:1 ratio to the trial arms. In the intervention arm, participants will watch a collage of three SAS videos underlining the importance of COVID-19 vaccination to provide study participants with access to evidence-based information regarding their risk of contracting and spreading the COVID-19 virus (arm 1: COVID-19 vaccine message) (23). In the APC arm, participants will watch a video that shows how important it is to help children find hope in the future (arm 2: no COVID-19 vaccine message) (24). In the control arm, participants will receive no intervention (arm 3: no video). Participants in arm 1 and arm 2 will not be able to pause or skip the video.

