**Figure 1 F1:**
[figure not shown]
Design of randomized controlled trials (second randomization is for a list experiment rather than for the group assignment). The order of the attention, knowledge, hope, and optimism questionnaires is sequential, since study participants complete them in succession. Inclusion criteria: Participants must be over the age of 18 (male, female, or other), have a current address in the United States, and be proficient in English.

After watching the video, participants will be asked to complete one attention question, four true/false knowledge questions about the COVID-19 vaccine, 14 Likert scaled questions about COVID-19 vaccine perceived risks and benefits, attitude, self-efficacy, and perceived norms, and 11 additional Likert scaled items indicating their level of hope and optimism. All questionnaires incorporating Likert scaled items were obtained from our prior research and are cited in the following sections that discuss the questionnaire items.

Furthermore, participants in each arm will be asked to complete five list experiments (25). For each list experiment, we randomized participants 1:1 to a control list or a treatment list. The control list consists of a list of four items about behavioral intent, which are unrelated to the COVID-19 vaccine. The treatment list consists of the same four list items as the control group, as well as a sensitive item assessing behavioral intent to get vaccinated and obtain additional information about COVID-19 vaccinations. The list experiment will be employed to decrease social desirability bias, as participants may already be primed to respond positively to questions about COVID-19 vaccines. Following completion of the list experiment, study participants will respond to seven questions regarding their level of trust in governmental bodies, institutions, and health care providers.

Study participants randomized to the APC group (arm 2) or the control group (arm 3) will be given the option to watch the COVID-19 vaccination intervention video as a post-trial access to treatment at the end of the experiment. The participants will be informed that they will not receive compensation for the time spent watching the SAS videos.

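### The secondary-factor analysis relates post-video scores to vaccination status alone, with no arm or status-by-arm term, so as written it does not answer the between-arm objective stated elsewhere in the protocol

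*Protocol article*

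**What the plan says.** The protocol article describes this comparison in several places, and they do not agree.

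- Introduction, secondary objective: to "explore the differences in individual factors connected to vaccine hesitancy between the three study arms after the interventions". This is a contrast between randomised arms.
- Abstract, Methods and analysis: the trial will measure the factors and "compare vaccinated and unvaccinated participants across the three arms". This is a contrast by status, made by arm.
- Secondary outcome measures: risk and benefit perception, social norms, hope and optimism are "secondary outcomes that we hypothesize will change as a result of the intervention".
- Statistical methods for primary and secondary outcomes: under the label of the second objective, "we will explore the differences in individual factors related to the levels of vaccine hesitancy between the vaccinated and unvaccinated study participants". A score is built for each of risk and benefit perception, attitude, self-efficacy, social norms and trust. Then: "We will then inspect correlations between such factors and participants' vaccination status using OLS models". No equation is given.

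On timing, Trial design says "After completing demographic, vaccine, and political beliefs surveys, participants will be randomly assigned to one of three arms", so vaccination status is fixed before allocation. The text after Figure 1 says "After watching the video, participants will be asked to complete one attention question", with the factor questionnaires following. On allocation: "We will randomize the participants in a 1:1:1 ratio to the trial arms".

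**The concern.** All four displayed models in the data analysis section (equations 1 to 4) carry a video-arm term. The factor analysis names only vaccination status. Followed literally, it has two consequences.

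First, the between-arm secondary objective has no stated analysis. The protocol expects the video to move several of these factors, but the planned regression contains nothing that could show it.

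Second, the status gap mixes participants who have just watched a persuasive vaccine video with participants who have not. The abstract's aim of identifying barriers and facilitators is naturally read as concerning the gap without the study's own video. A single gap over all arms answers that question only if the video moves vaccinated and unvaccinated people equally. Without a status-by-arm term, nobody can tell whether it does.

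**Working it through.** The documents give no sample size, power or effect figure for this analysis, so there is no stated figure to reproduce.

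**Inputs from the protocol.** N = 10,000; allocation 1:1:1, so one third see the SAS video; status recorded before randomisation; scores recorded after the video.

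**Assumptions.** Factor SD = 1. The attention placebo (APC) video has no effect on the factors. The unvaccinated share is not stated. I use 20%, and also 10.9%, the introduction's figure for hesitant US adults at the end of 2021, as a proxy. The difference in video effect between status groups is varied from 0.1 to 0.3 SD.

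**Step 1: what a pooled gap estimates.** Let G0 be the vaccinated-minus-unvaccinated gap without the SAS video, and eV and eU the video effects in the vaccinated and unvaccinated. Arm is randomised independently of status, so

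E[pooled gap] = G0 + (eV - eU)/3.

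- Equal effects: (eV - eU)/3 = 0, no shift.
- Differential 0.1 SD: 0.1/3 = 0.033 SD.
- Differential 0.2 SD: 0.2/3 = 0.067 SD.
- Differential 0.3 SD: 0.3/3 = 0.10 SD.

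The sign follows eV - eU.

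**Step 2: simulation check** (G0 = 0.5, 10.9% unvaccinated, 600 replicates). Equal effects of 0, 0.1 and 0.3 SD gave pooled gaps of 0.500, 0.502 and 0.501. Unequal effects (eV, eU) gave: (0.1, 0.2) 0.469; (0, 0.2) 0.434; (0, 0.3) 0.400; (0.2, 0.1) 0.534. Adding an arm main effect alone left these values essentially unchanged. Using only the two arms without the SAS video returned about 0.50 every time.

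**Step 3: shift against precision, 20% unvaccinated.**

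- All arms: SE = sqrt(1/2000 + 1/8000) = 0.025.
- Arms 2 and 3: SE = sqrt(1/1333 + 1/5333) = 0.031, which is sqrt(3/2) = 1.2 times the pooled SE.
- Arm 3 alone: SE = sqrt(1/667 + 1/2667) = 0.043, which is sqrt(3) = 1.7 times.

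For a 0.2 SD differential, shift/SE = 0.067/0.025 = 2.67. A pooled 95% interval covers the no-SAS-video gap with probability Phi(1.96 - 2.67) - Phi(-1.96 - 2.67), about 24%.

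| Assumed differential | Shift in pooled gap | Coverage, 20% unvaccinated (SE 0.025) | Coverage, 10.9% unvaccinated (SE 0.032) |
|---|---|---|---|
| 0 | 0 | 95% | 95% |
| 0.1 SD | 0.033 | about 73% | about 82% |
| 0.2 SD | 0.067 | about 24% | about 45% |
| 0.3 SD | 0.10 | about 2% | about 12% |

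**Step 4: which estimate is better overall, 20% unvaccinated.** At a 0.1 SD differential the pooled RMSE is sqrt(0.033^2 + 0.025^2) = 0.042, against 0.043 for arm 3 alone and 0.031 for arms 2 and 3. At 0.2 SD the pooled RMSE is sqrt(0.067^2 + 0.025^2) = 0.071, against the same 0.043 and 0.031.

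**The case against.** The strongest reply is that the model is inferred from silence. The sentence on correlations gives no equation, does not say that arms are pooled, and does not exclude an arm term. The abstract speaks of all three arms, and the study timeline mentions a pre-analysis plan that is not shown. That is fair as regards model detail. It does not remove the conflict: the data analysis section fixes a contrast (status) and a method (OLS), and that contrast is not the one the introduction sets as the secondary objective.

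A reader might go further and infer that the reported gap is biased because a third of the sample has seen the video, and that a more effective video would hide more of the barriers. The documents do not support this. Status precedes randomisation, so a common video effect cancels. A shift needs an effect that differs by status, and the protocol hypothesises change, not differential change. No passage says that vaccinated people are near ceiling; the introduction notes hesitancy among the fully vaccinated too. If the vaccinated respond more, the gap widens. Nor does any passage name the no-video gap as the target, and a gap averaged over randomised arms is a valid quantity if described as such.

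The coverage figures rest on assumed differentials. It also stands that making arm 3 alone the headline is not clearly better: at 0.1 SD it gains nothing over pooling. Of the five scores analysed, only two (risk and benefit perception, social norms) are among the factors expressly hypothesised to change.

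**Conclusion.** The point holds as an inconsistency between the objective and the analysis, with a conditional consequence for interpretation. As written, the factor analysis does not test differences between arms and cannot separate the status gap in SAS viewers from that in non-viewers. A gap pooled over arms is unbiased for the no-SAS-video gap if the video effect is the same in both status groups. Otherwise it differs by one third of the differential, in either direction: 0.033 to 0.10 SD for assumed differentials of 0.1 to 0.3 SD. Those sizes assume an inert APC video; how much they matter relative to the SE depends also on the unvaccinated share, which the protocol does not state. It is not established that the gap will be biased, or that barriers will be understated. The analysis is secondary and exploratory, so this should be corrected but does not threaten the primary outcomes.

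**What to change.** In the section on statistical methods for primary and secondary outcomes, replace the sentence on correlations with a model of each factor score on vaccination status, arm and status x arm. From it, report the between-arm differences, the status gap within each arm and the interaction. Label any gap pooled over arms as an average over participants who did and did not see the SAS video. Bring the abstract, introduction and analysis section into line on what the secondary objective is. Hope and optimism are named as secondary outcomes but are missing from the scores listed for analysis, so state whether the same model applies to them.

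If a no-SAS-video gap is wanted for the barriers and facilitators aim, take it from the same model: from arm 3, or from arms 2 and 3 if the APC video is taken as inert for these factors. State the choice in advance.

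The cost is a few sentences and no new data. The no-SAS-video gap has a larger SE than the pooled one, about 1.2 times for arms 2 and 3 and 1.7 times for arm 3 alone. Further covariates are not needed for this correction.
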